### Coping questionnaire

Participants are asked to rate the frequency and perceived helpfulness of 26 coping strategies for depression symptoms over the past month at baseline and at post intervention. The coping strategies include the 14 used in the Mood Memos emails, as well as other strategies that were rated in the expert study [10] as relatively unhelpful (e.g., *you drank alcohol*) or unlikely to be helpful (e.g., *you had a warm bath*). These were assessed to determine participants' coping repertoire at baseline, whether the intervention changed their coping strategies, and whether this was related to intervention response. Frequency of use is rated on a 5-category scale (*not at all*, *infrequently*, *moderately frequently*, *very frequently*, *don't know*), and perceived helpfulness on a 5-category scale (*not at all helpful*, *a little helpful*, *moderately helpful*, *very helpful*, *don't know*). Participants are asked to rate a strategy's perceived helpfulness only if they have indicated they had used the strategy (*infrequently *to *very frequently*) in the past month.

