### Statistical analysis

Primary effectiveness analyses will be undertaken on an intention-to-treat basis. Any participants who were randomised but who withdraw from the study, or who take up alternative treatments, will be included in the analysis as randomised. Continuous outcomes (PHQ-9 scores, K10 scores, WSAS scores) will be evaluated using mixed models for repeated measures (MMRM) [68]. This method of analysis will be utilised because of its ability to include participants with missing data under the assumption that observations are missing at random (MAR). The inclusion of an additional measurement occasion halfway through the intervention should increase the tenability of the MAR assumption. *A priori *contrasts will compare change from baseline at the primary endpoint (post-intervention) and at 6-months follow up. Dichotomous outcomes will be defined. These include the development of probable major depression (as indicated by PHQ-9 results) in participants who did not meet this criterion at baseline and remission from sub-threshold depression in those who fell into this category at baseline. Relative risk will be calculated and tested for significance. The numbers needed to treat to avoid one person developing major depression and to achieve one remission from sub-threshold depression will be calculated.

In addition to intervention group, a number of variables will be examined to see if they predict outcomes: age, gender, education level, past diagnosis of depression, past diagnosis of psychotic disorder, whether they sought help during the intervention, baseline self-help for depression self-efficacy, and whether they had experienced an adverse life event in the six months prior to the development of sub-threshold depression.

Other outcomes include coping strategies used, knowledge of depression, and self-help for depression self-efficacy. In order to determine whether any change in depression might be due to changes in coping behaviour, the coping strategies used by participants will be evaluated. Usage rates and change in usage of each strategy in each intervention group will be compared pre- and post-intervention. Change in use of each strategy will be evaluated using logistic regression expressed as odds ratios with their 95% confidence intervals. Each strategy's mean perceived helpfulness for participants using them will also be compared pre- and post-intervention between groups.

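### The named coping analyses do not relate coping to PHQ-9, although that is their stated purpose, and the post-intervention helpfulness comparison among users is not a randomised comparison

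*Protocol article*

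**What the plan says.** The Protocol article, Statistical analysis, gives the purpose of the coping work as finding out "whether any change in depression might be due to changes in coping behaviour". It then names three analyses:

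- A description of use by arm: "Usage rates and change in usage of each strategy in each intervention group will be compared pre- and post-intervention".
- A regression for every strategy, with use and not depression as its outcome: "Change in use of each strategy will be evaluated using logistic regression expressed as odds ratios with their 95% confidence intervals".
- A comparison of ratings restricted to users: "mean perceived helpfulness for participants using them will also be compared pre- and post-intervention between groups".

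The Coping questionnaire section lists 26 strategies, 14 of them used in the emails, rated at baseline and post-intervention with a one-month recall. It adds a restriction: "Participants are asked to rate a strategy's perceived helpfulness only if they have indicated they had used the strategy". It also repeats the aim of relating coping change to intervention response, without naming an analysis.

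In Statistical analysis, PHQ-9 is analysed by MMRM, with post-intervention as the primary endpoint. The listed predictors of outcome include baseline self-efficacy and adverse life events, but neither coping use nor its change.

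**The concern.** Two things do not fit together.

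First, the stated question joins coping change and depression change, but no named analysis contains both. Followed as written, the plan would answer a question about mechanism with a list of odds ratios for use, set beside a separate PHQ-9 result.

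Second, the active emails are designed to make people take up strategies. After the intervention, the users of a strategy in the active arm may therefore be a different kind of person from the users in the control arm. A difference in their mean ratings may reflect who started using the strategy and not how well it worked. A strategy that reaches more people could even look less helpful in the active arm.

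At stake is the interpretation of a mechanistic aim, which is neither the primary nor a listed secondary outcome.

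**Working it through.** The article gives no figure for the coping analyses, so there is none to reproduce. It also gives no usage rates, so all usage and helpfulness inputs below are assumptions.

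**1. Can the named outputs show the link?** Assume that 55% of the active arm and 40% of the control arm use a strategy, and that the arms differ by -0.20 SD on PHQ-9. Consider two extreme cases.

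- *Full mediation.* Use lowers PHQ-9 by 0.20/0.15 = 1.33 SD, and arm has no other effect. The arm difference is -1.33 × (0.55 - 0.40) = -0.20 SD.
- *No mediation.* Arm lowers PHQ-9 by 0.20 SD directly, and use has no effect.

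In both cases the odds ratio for use is (0.55/0.45)/(0.40/0.60) = 1.83. A simulation of 1,000,000 participants gave:

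| | Full mediation | No mediation |
|---|---|---|
| Odds ratio for use | 1.82 | 1.84 |
| PHQ-9 arm difference | -0.20 SD | -0.20 SD |
| PHQ-9 arm difference within users | 0.00 SD | -0.20 SD |

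The first two rows are what the plan would report, and they agree apart from simulation error. Only the third row, which uses coping and PHQ-9 together, separates the cases. It does so cleanly here because the simulation has no confounding of use.

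**2. Selection among users, with no true effect on helpfulness.** Give every participant a standard-normal helpfulness with the same distribution in both arms. Let the log-odds of use be slope × helpfulness, plus 0.2 (active) or minus 0.4 (control).

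| Slope | Use, active | Use, control | Active minus control among users |
|---|---|---|---|
| 0 | 55.0% | 40.2% | 0.00 SD |
| 0.5 | 54.7% | 40.6% | -0.07 SD |
| 1.0 | 54.0% | 41.8% | -0.10 SD |

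**3. An illustration in scale points.** Score helpfulness 0 to 3. Suppose that 30% of each arm already use a strategy (mean 2.0) and the active emails recruit a further 20%.

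- If new users average 1.2, the active user mean is (0.30 × 2.0 + 0.20 × 1.2)/0.50 = 1.68, against 2.00 in control: a difference of -0.32.
- In general the difference is (0.20/0.50) × (new-user mean - 2.0). It is -0.16 if new users average 1.6, and 0 if they average 2.0.
- With non-users scored 0, total helpfulness per participant is 0.84 in the active arm and 0.60 in control. The user mean points the other way.

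**4. Number of odds ratios.** With independent tests at 5%:

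- All 26 nulls true: 26 × 0.05 = 1.3 false positives expected; chance of at least one 1 - 0.95^26 = 74%.
- All 14 promoted strategies truly change, so 12 nulls remain: 12 × 0.05 = 0.6 expected; chance of at least one 1 - 0.95^12 = 46%.

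**5. Timing.** The only post-baseline coping measure (Protocol article, Table 2) falls at the same assessment as the primary PHQ-9. The recall windows, one month for coping and two weeks for PHQ-9, overlap. The 6-month PHQ-9 comes clearly after the coping measure.

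**The case against.** The link is intended: the Coping questionnaire section says so, and a fuller plan might name the model. The purpose is worded cautiously, and a difference in use between arms is a necessary first step whose absence would count against the mechanism. This stands in part. A reader might infer that the usage analysis is worthless or that no linking analysis exists anywhere; the article supports neither. But it does more than stay silent: it states a purpose and then names analyses that cannot meet it.

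The helpfulness mean is openly described as being for users, and non-users cannot rate a strategy. As a description of users it is correct. A reader might also infer that all the planned ratings come from groups selected after randomisation. They do not: baseline raters are users before randomisation, and the problem lies in the post-intervention ratings and in change between the two. Nor do the documents establish a bias of any given size, since it is zero if use is unrelated to helpfulness.

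On multiplicity, the article plans confidence intervals for the odds ratios and states no significance rule for them. A reader might infer that a false-positive strategy is probable. That needs most of the 26 nulls to be true, which would mean the emails changed little of what they promote.

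**Conclusion.** The point holds in limited form. The named analyses can show whether the emails changed coping, but not whether coping change accounts for depression change. Under the assumed inputs, full and no mediation give the same reported results (odds ratio about 1.8, PHQ-9 difference -0.20 SD).

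The post-intervention comparison of user means between arms is not a randomised comparison. Its bias may be nil. It was 0.00 to -0.10 SD in the simulation and -0.32 points in the separate illustration, and both size and sign depend on how use relates to helpfulness. The chance of at least one false positive among the odds ratios, if each were tested independently at 5%, is 46% with 12 true nulls and 74% with 26.

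A reader might infer that the trial's efficacy conclusion is weakened. It is not: the PHQ-9 analysis by randomised arm does not depend on any of this.

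**What to change.** 1. **Helpfulness.** Label mean helpfulness among users as descriptive. Make the comparison between arms in all assessed participants, on a yes/no outcome of having used the strategy and found it at least moderately helpful, adjusted for the baseline answer. State how don't-know answers count. Show it beside the usage comparison, because this outcome rises with use alone. It still depends on who completes the post-intervention assessment.
2. **Link to depression.** Define one index over the 14 promoted strategies and compare it between arms, adjusted for its baseline value. Then fit a mediation model from arm to post-intervention index to 6-month PHQ-9, adjusted for baseline index and baseline PHQ-9. State the assumption of no unmeasured confounding. Give the version that also adjusts for post-intervention PHQ-9 only as a sensitivity analysis: it helps with temporal order, but it removes any coping effect already present at 6 weeks and could hide a real mechanism.
3. **Odds ratios.** Call the 26 per-strategy odds ratios descriptive.

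If the second step is not wanted, limit the aim in the Coping questionnaire and Statistical analysis sections to whether the emails changed coping.

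The cost is extra analysis of data already planned for collection, and reliance on a mediation assumption that cannot be tested.

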## Discussion

This study is part of a wave of new internet interventions to manage disease and improve health behaviour. Public health interventions disseminated via the internet have the potential for great impact by reaching large populations and providing an interactive and tailored intervention. As people from all over the world can be recruited, internet-based trials have the potential for large sample sizes and improved external validity [70]. Although initial set-up costs may be relatively high, the scalability of internet interventions means lower overall costs for large samples, particularly if data collection is completely internet-based. Automating data collection and outcome measurement also minimises the potential for biases introduced by human observers, and ensures the uniformity of intervention delivery [70]. The study's unique strengths are its promotion of self-help strategies endorsed by expert consensus and its use of messages designed with input from theories of behaviour change and persuasion. Another strength of the study is the use of a content-relevant attention placebo control condition, rather than a waitlist or no-contact control group, as is often used in depression prevention research [18]. This eliminates the possibility of placebo effects accounting for any intervention effects found.

Automating study processes and setting the intervention on the internet has a number of advantages, but also presents several challenges. Internet interventions frequently demonstrate high non-usage attrition and high dropout attrition [41] due to less participant supervision and ease of discontinuing. Dealing with attrition and missing data is a fundamental methodological challenge. Fully automated online interventions can be subject to multiple enrolments, which may bias randomisation [71], however this is less of a problem in studies that do not provide financial incentives for participation. In addition, there are strategies to detect multiple enrolments, such as analysing similar or identical IP addresses and usernames [69]. Unequal access to the internet in the community is frequently cited as a criticism and challenge to external validity [72]. However, the study is a first test of the value of email-based self-help messages for depression, and is not proposed as the only solution, nor a solution that will benefit everyone in the community.

Conducting assessments of outcomes on the web also poses several limitations. There are concerns about the equivalence in validity and reliability of web-based assessments to paper-and-pencil based assessments [73], though when this has been evaluated with depression or mental health assessments there is little evidence of differences between the two administration modes [74,75]. In addition, all outcome measures are self-rated by definition, rather than the preferred method of clinical ratings or diagnostic interviews. Self-rated assessment may be vulnerable to respondent bias [76] and other causes of depression (e.g., medication side effects, physical diseases) cannot be ruled out as would occur in a diagnostic interview, nor are co-morbid mental disorders assessed. However, the study asks participants at baseline about bereavement and history of mania or psychotic disorders. The presence of these could be used in a sensitivity analysis. We decided not to exclude individuals with these profiles from participating, because we wanted to test whether the approach is feasible and effective as a first step, so we kept exclusion criteria to a minimum.

Limited research suggests that email-based interventions are a promising method of delivering health behaviour change interventions. In contrast to website-based interventions, email-based interventions may be more convenient to participants because they do not have to take conscious action in order to receive content. These interventions have the advantage of *stickiness *[77,78], the concept that ideas and intentions are more likely to 'stick' (i.e. make an impact and be remembered) when they appear frequently in the person's environment. They are also potentially easier to implement than complex website-based interventions and hence could have better cost-effectiveness. Website-based depression interventions can be effective but require considerable user commitment and usually health professional involvement [79]. If the email-based approach used in this study proves effective, the Mood Memos intervention could be broadly disseminated and be a low-cost way of reducing the population burden of depressive symptoms.
